This study is collecting data on births to all women in 26 UK maternity units from 2015 and is identifying the numbers, proportion and characteristics of women who use water immersion during labour or birth. The study will also establish whether waterbirth is as safe for mothers and their infants as using a pool during labour but getting out prior to birth. Data will be collected on 15 000 waterbirths and 15 000 land births among women with uncomplicated pregnancies from National Health Service (NHS) sites which use Wellbeing Software’s (WS) maternity software system EuroKing. This study will use data recorded routinely as part of standard maternity care and stored on respective NHS site’s servers. For infants admitted to a neonatal unit (NNU), the study will also use data held by the National Neonatal Research Database (NNRD). Data needed to answer some study questions are already recorded, for example, perineal trauma, therefore, data from births from 2015 onwards can be included. Existing, routinely collected data does not capture all information to answer the study questions, data items missing from existing routinely collected data include infants receiving antibiotics without admission to NNU and whether following waterbirth the placenta is delivered in or out of water. Cardiff University (CU) has worked with WS in order to develop study specific data fields which will enable these data to be captured in participating sites from 2019 onwards.

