### Secondary objectives

To establish:

Overall proportion and characteristics of women who use a pool for labour or birth, compared with those who do not use a pool.Characteristics of, and outcomes for, women with risk factors, who use a pool during labour.Characteristics of, and outcomes for, women who develop labour complications who use a pool during labour.Factors associated with rates of pool use in individual maternity units.

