#### Infant primary outcome

A composite of ‘adverse infant outcomes or treatment’ to include:

Any NNU admission requiring respiratory support.Antibiotic administration within 48 hours of birth (with/without culture proven infection).Intrapartum stillbirth or all deaths prior to NNU/postnatal ward discharge.

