### Qualitative component

The aim of the qualitative component of the study is to identify and explore factors which influence the use of birth pools and giving birth in water.

Phase 1:

Six closed online discussion groups hosted on the CU website and telephone interviews:

Women with recent experience of maternity services.Heads of midwifery and midwifery managers.Consultant midwives.Band 5/6 clinically focused midwives.Obstetricians.Neonatologists and paediatricians.

Phase 2:

In-depth organisational case studies across three study sites, comprising midwifery-led and obstetric units with a range of waterbirth rates. Data points:

Key documents, online information and existing data relating to pool use and waterbirth.Information relating to unit equipment and facilities.Group or individual discussions with staff and lay representatives.

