### Recruitment/opt-out

For the cohort study, data will be collected on all women and babies born at participating sites from 1 January 2015 until study end date unless they choose to opt-out of the study.

The online discussion groups will be advertised via social media, magazine articles, email circulation and leaflets/flyers handed out at conferences. Adverts will provide a brief overview of the discussion groups and a website link which will contain study overview, a participant information sheet (PIS) and discussion group ground rules. If keen to participate, individuals will submit their email address via the website, which will generate an automated email invitation with a link to the discussion group registration page. Participants will be asked to complete an online consent form, create an anonymous public forum name and password to log in to the discussion, and click to confirm that they agree to comply with the discussion group ground rules.

The telephone interviews will be advertised via professional and lay networks, including social media and email circulation. Adverts will provide a brief overview of the study and the purpose of the interviews, together with a contact email address for those interested in taking part. Potential participants will be emailed a copy of the PIS and given the opportunity to ask questions. Those who would like to take part will be asked via email to agree a date for the interview.

For phase 2 of the qualitative work, data provided by sites will be used to identify midwifery-led and obstetric units, enabling the team to work with sites with both low and high waterbirth rates. Once potential sites are identified, the site Principal Investigator (PI) will be contacted by a member of the study team, provided with information about the case studies and invited to take part. For the discussions within the case study sites, the study will be publicised at unit meetings and via local networks, and potential participants requested to contact the research team to receive information. Researchers will also approach staff members and lay representatives directly to encourage voluntary participation. A PIS and opportunity to ask questions will be provided. Those who would like to take part will be asked to contact the researchers to arrange to participate in a discussion.

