### Main analysis

Primary analysis will compare maternal and infant outcomes only between women without identified pregnancy or intrapartum complications ‘low risk’ who stay and give birth in the pool (waterbirth, group 1) compared with women without identified pregnancy or intrapartum complications ‘low risk’ who use water immersion during their labour but decide to leave the water for birth (out of water, group 2).

The primary analyses are based on a non-inferiority test of birth in water vs on land, comparing (1) the proportion of mothers that have OASIS (based on retrospective and prospective EuroKing data) and (2) the proportion of infants with a composite outcome of ‘adverse infant outcome or treatment’ (based on prospective EuroKing and NNRD data).

To test the primary hypothesis of non-inferiority between birth in water and on land, the maternal and infant primary outcomes will be evaluated for non-inferiority using logistic regression models, in the first instance with no adjustment for covariates. Adjusting for potential confounders may result in a more precise treatment effect estimate. The potential confounders of both primary outcomes (listed in table 2) will be considered. Directed acyclic graphs; visual representations of causal assumptions will be used to identify the presence of confounders.

**Table 2 T2:** Potential confounders for both maternal and infant primary outcomes

	**Maternal outcome: OASIS**	**Adverse infant composite outcome**
Maternal age (years)	X	X
Maternal BMI	X	X
Parity	X	
Duration of labour	X	X
Gestational age at delivery (weeks)	X	X
Birth weight (g)	X	X
Infant head circumference (cms)	X	
Maternal thyroid disease (including hypothyroidism)		X
Prelabour ruptured membranes		X
Intrapartum fever		X
Small for gestational age (weight <10th centile for gestational age)		X
Infant gender		X
Meconium-stained liquor		X

BMI, body mass index; OASIS, Obstetric Anal Sphincter Injury.

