The main logistic model will incorporate these selected covariates through regression adjustment. Results will be reported as an unadjusted and adjusted ORs (comparing birth in water to on land), and a two-sided 90% CI for the unadjusted and adjusted OR will be calculated. Non-inferiority will be concluded if the upper limit of the 90% CI for the difference in infant outcome between the groups is less than 1.0% (OR <1.21). Similarly, for the mother’s outcome, non-inferiority will be concluded if the upper limit of the 90% CI for the difference in the proportion of OASIS between the groups is less than 1.0% (OR <1.23) in nulliparous low-risk women and less than 0.6% (OR <1.38) in parous low-risk women. The data will then be combined to assess the effects averaged across both strata.

If non-inferiority is shown, then superiority analysis will be conducted as secondary analysis of the primary outcomes using logistic regression and will be presented as (unadjusted and adjusted) OR of outcomes in the waterbirth group compared with the birth on land group. Parameter estimates will be provided alongside 95% CI and p value. Secondary outcomes will have non-inferiority testing as detailed above.

Secondary analysis will describe the type and rates of complications among (a) low risk women who left the pool due to clinical need along with the associated maternal and infant outcomes and (b) high risk women using a pool, along with associated care (for example use of waterproof CTG cardiotocography), and maternal and infant outcomes

Maternal characteristics such as age, parity and ethnicity of all women giving birth in the study sites during data collection will be obtained and the characteristics of women who do and who not use a pool during labour, will be compared and described.

All telephone and face-to-face discussions in phase 1 and phase 2 will be audiorecorded and transcribed verbatim. For phase 1 of the qualitative component, framework analysis will be undertaken to generate key hypotheses for further exploration in phase 2. In phase 2, data will be thematically analysed initially, supported by NVivo, in order to develop an analytic framework, which will then be used to code all data.

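### The candidate confounder list omits maternity unit and year of birth, so differences between units could confound both primary comparisons in either direction

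*Protocol article*

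**What the plan says.** The Main analysis section introduces the candidates with "The potential confounders of both primary outcomes (listed in table 2) will be considered". It adds that, in directed acyclic graphs, "visual representations of causal assumptions will be used to identify the presence of confounders". It then states: "The main logistic model will incorporate these selected covariates through regression adjustment".

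Table 2 has 13 rows: maternal age, BMI, parity, duration of labour, gestational age, birth weight, head circumference, thyroid disease, prelabour ruptured membranes, intrapartum fever, small for gestational age, infant gender and meconium-stained liquor. No row is a unit, a place or a date, and the analysis text names none elsewhere.

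Other sections bear on this:
- Introduction: "This study is collecting data on births to all women in 26 UK maternity units from 2015".
- Qualitative component: the case study sites are described as "comprising midwifery-led and obstetric units with a range of waterbirth rates". Recruitment/opt-out says that site data will be used to choose sites, "enabling the team to work with sites with both low and high waterbirth rates".
- Infant primary outcome: one component is "Antibiotic administration within 48 hours of birth (with/without culture proven infection").
- Study design and Main analysis: OASIS uses retrospective and prospective births from January 2015. The infant composite uses births from each site's own opening date.

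**The concern.** A factor confounds when it is tied to both exposure and outcome. For unit, the article itself points to the exposure side: waterbirth rates differ between units. The outcome side is reasoning rather than text. Giving antibiotics without proven infection is a treatment decision that can follow local policy, and detection of OASIS may differ with local practice. If both links hold, part of the water-versus-land contrast is a contrast between units, and no set of individual characteristics need remove it.

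The margins are narrow: 1.0 point for OASIS in nulliparous women, 0.6 in parous women and 1.0 for the infant composite. A few tenths of a point from unit mix is a sizeable part of any of them.

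The stated limitation is unmeasured confounding. Unit is not unmeasured, because extracts are made from each participating site's server.

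Year of birth matters in the same conditional way, chiefly for OASIS. If the share staying in the water and the OASIS rate both drift over the years, pooling from 2015 mixes that drift into the comparison.

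**Working it through.** **1. The plan's own figures reproduce.** Inputs are from Sample size: 90% power, one-sided 5%, no true difference. The formula is n per group = (1.645 + 1.282)² × 2p(1−p)/margin², where the squared term is 8.564.
- Nulliparous: 8.564 × 2 × 0.046 × 0.954 / 0.01² ≈ 7517 (stated 7500).
- Parous: 8.564 × 2 × 0.016 × 0.984 / 0.006² ≈ 7491 (stated 7500).
- Infant: 8.564 × 2 × 0.05 × 0.95 / 0.01² ≈ 8136 (stated 8100).

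The margin odds ratios come out at 1.230, 1.383 and 1.213, against the stated 1.23, 1.38 and 1.21. There is no arithmetic error in the design.

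**2. Model for the bias.** Assumptions, none of them in the article: two sets of units with equal numbers of low-risk pool users; shares w1 and w2 giving birth in water; outcome rates r1 and r2 that depend on the unit only; no effect of water; unit left out of the model.
- Water risk = (w1·r1 + w2·r2)/(w1 + w2)
- Land risk = ((1−w1)·r1 + (1−w2)·r2)/(2 − w1 − w2)

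**3. Infant composite, r1 = 4% and r2 = 6% (average 5%, as planned).**
- Shares 60/50: water 5.4/1.1 = 4.91%, land 4.6/0.9 = 5.11%, difference −0.20 points.
- Shares 70/40: water 5.2/1.1 = 4.73%, land 4.8/0.9 = 5.33%, difference −0.61 points.

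The planned standard error is √(2 × 0.05 × 0.95/8100) = 0.342 points. If the true difference equals the margin, the chance of wrongly declaring non-inferiority is Φ(−1.645 + bias/SE):
- 60/50: Φ(−1.645 + 0.202/0.342) = 15%.
- 70/40: Φ(−1.645 + 0.606/0.342) = 55%.

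The nominal value is 5%. With the standard error taken at 5% v 6% instead, √((0.0475 + 0.0564)/8100) = 0.358 points, these become 14% and 52%.

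**4. Opposite sign.** If the units with more waterbirth have the higher rate (6% v 4%), the differences are +0.20 and +0.61 points. Power with no true effect is Φ((1.0 − bias)/0.342 − 1.645), that is 75% and 31% instead of 90%.

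**5. OASIS, with another assumed set: shares 60/40, rate 1.5 times higher where waterbirth is commoner.**
- Nulliparous: rates 5.52% and 3.68%; water 4.784%, land 4.416%; difference +0.37 points, 37% of the margin. Power falls to 58%.
- Parous: rates 1.92% and 1.28%; water 1.664%, land 1.536%; difference +0.13 points, 21% of the margin. Power falls to about 74%.

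**6. Null case.** If w1 = w2 or r1 = r2, the bias is exactly zero. The article does not exclude this.

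**7. Events available for adjustment.** Nulliparous 15 000 × 4.6% = 690; parous 15 000 × 1.6% = 240; infant 16 200 × 5% = 810. Fixed effects for 26 units (25 terms) and six years (5 terms), plus the six OASIS covariates other than parity at one term each, make 36 terms. In the parous stratum that is 240/36 ≈ 6.7 events per term.

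**The case against.** The strongest reply is that this is a condensed article. Table 2 is a list of potential confounders, causal graphs will do the selecting, and an analysis plan not shown may handle site. That carries some weight: the graphs could in principle bring in unit. But the candidates are named, and the model takes its covariates from them. A published list that leaves out a whole class of measured factor is a stated choice, so it should be corrected, or reconciled with the analysis plan if that differs.

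Several stronger readings are tempting and not supported:
- **That the plan treats births within a unit as independent.** The article is silent on clustering, and variance estimation is commonly left to the analysis plan.
- **That the study's own objective proves the exposure link.** The objective is "Factors associated with rates of pool use in individual maternity units". Everyone in the primary comparison used a pool. What matters is the share of low-risk pool users who stay in for birth, and no figure by unit is given. The passages on waterbirth rates refer to overall rates, which mix pool uptake with staying in.
- **That unit policy does bias the result.** No passage reports outcome or treatment rates by unit. Only that it could is supportable.
- **That new fields at site opening distort OASIS.** OASIS was already recorded throughout. The new fields include risk status at pool entry and reasons for pool exit, which bear on group membership. That is possible misclassification, which a year term would not repair.
- **That within-unit comparison is free because every unit supplies both groups.** Eligibility requires only the software and waterbirth facilities. Overlap is likely but not stated, and the parous stratum has few events.

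**Conclusion.** The point holds as a weakness in a stated adjustment list. Unit and year of birth are missing from the candidates for both primary models, while the article itself expects waterbirth rates to differ between units and includes an outcome component open to local treatment policy. The direction is unknown: the omission could produce false non-inferiority or hide true non-inferiority.

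Its size cannot be taken from the article. The 0.2 to 0.6 points for the infant composite rest wholly on the assumed shares and rates, and zero is also compatible with the text. The illustration shows only that moderate differences between units would matter against margins of 0.6 to 1.0 point. The stated sample sizes are not affected. The change is worth making; the omission does not by itself invalidate the design.

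**What to change.** Add maternity unit and year of birth to both columns of Table 2 and to both adjusted primary models, within each parity stratum for OASIS.

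For unit, condition on site or use a random intercept rather than fit a separate term per site, because about 240 events are expected among parous women (roughly 9 per unit if spread evenly over 26). Conditioning uses within-unit contrasts only. A random intercept still borrows some between-unit information, so if it is chosen, report a site-conditioned estimate beside it.

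Include birth setting (obstetric, alongside or freestanding midwifery unit) only as the setting planned at labour onset, and only if recorded. Actual setting may follow from leaving the pool, and adjusting for it could condition on a consequence of exposure.

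If the full analysis plan already handles site, align Table 2 with it. Extraction by site makes unit available, and the planned sample size need not change. The cost is a small loss of precision, mainly in the parous stratum, and the loss of any unit that contributes only one group if conditioning is used.

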### Analysis

#### Sample size

The non-inferiority of birth in water compared with birth on land on rates of OASIS will be examined by parity. The Birthplace in England study found that overall 4.6% and 1.6% of nulliparous and parous women respectively, sustained OASIS.^10^ A sample size of 15 000 nulliparous and 15 000 parous low-risk women (7500 each water and land) is required to obtain 90% power, and a 95% one-sided CI around a treatment difference of zero. A non-inferiority margin of 1% or less, and 0.6% or less will be taken as clinically non-significant among nulliparous and parous low-risk women, respectively. Since nulliparous women birthing in water are regarded as the least prevalent of the four groups, the data collected would provide data on 7500 would ensure adequate numbers in the other three, more prevalent groups. These data will be combined to assess the effects averaged across both strata at an increased power, with a sample size of 30 000 low-risk women. We have assumed that 25% of the 6600 waterbirths recorded in EuroKing in 2015 were nulliparous women (1650/annum). For the infant primary outcome, an estimate of 5% is used for the proportion of infants born to low-risk mothers experiencing ‘adverse infant outcome or treatment’.^11^ A non-inferiority margin of 1.0% or less will be taken as clinically non-significant. A sample size of 16 200 infants (8100 per group water/land) are required to have 90% power, and a 95% one-sided CI around a treatment difference of zero.

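### Each primary non-inferiority rule carries a difference limit and an odds-ratio limit as if they were the same; they agree only at the assumed land rates, and the stated 90% power belongs to the difference

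*Protocol article*

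**What the plan says.** **Sample size section.** The margins are absolute: 1.0 percentage point for OASIS in nulliparous women, 0.6 in parous women and 1.0 for the infant composite. The planning rates are "overall 4.6% and 1.6% of nulliparous and parous women respectively, sustained OASIS", and for infants "an estimate of 5% is used for the proportion of infants born to low-risk mothers experiencing" the composite outcome. Each maternal stratum "is required to obtain 90% power, and a 95% one-sided CI around a treatment difference of zero" with 7500 women per group; the 8100 infants per group "are required to have 90% power, and a 95% one-sided CI around a treatment difference of zero".

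**Main analysis section.** Non-inferiority is evaluated with logistic regression. Results are reported as ORs, and "a two-sided 90% CI for the unadjusted and adjusted OR will be calculated". The next sentence places the infant criterion on another scale: the "upper limit of the 90% CI for the difference in infant outcome between the groups is less than 1.0% (OR <1.21"). The maternal rules follow the same pattern: a difference below 1.0% (OR below 1.23) for nulliparous women and below 0.6% (OR below 1.38) for parous women.

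**The concern.** Each primary test has two thresholds presented as one. A fixed risk difference and a fixed OR correspond at a single control rate only, so the same data can pass one limit and fail the other. The article does not say what happens then. The criterion names a difference, while the announced output is an OR with its interval, so an analyst could in good faith hold that output against the bracketed limit.

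Two things are at stake. First, the clinical margin: at a land rate above the assumed one, the OR limit lets through an excess larger than the absolute margin; at a lower rate it is stricter than intended. Second, the power: the study was sized on the difference, and the stated 90% does not carry over to a decision made on the OR.

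**Working it through.** **Inputs** (Sample size and Main analysis sections): rates p = 4.6% (nulliparous), 1.6% (parous), 5% (infant); margins d = 1.0, 0.6, 1.0 points; n = 7500, 7500, 8100 per group; one-sided 5%, so z = 1.645; power 90%, so z = 1.282; true difference zero; OR limits 1.23, 1.38, 1.21.

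**1. The plan's sample sizes reproduce on the difference.** n per group = 2p(1−p)(1.645 + 1.282)²/d².

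- Nulliparous: 2 × 0.043884 × 8.564/0.010² gives 7517.
- Parous: 2 × 0.015744 × 8.564/0.006² gives 7491.
- Infant: 2 × 0.0475 × 8.564/0.010² gives 8136.

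These agree with 7500, 7500 and 8100. Power at the stated sizes is 89.9%, 90.0% and 89.9%.

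**2. The bracketed ORs are the margins converted at the planning rates.** OR = [(p+d)/(1−p−d)]/[p/(1−p)].

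- 4.6% to 5.6%: 1.230.
- 1.6% to 2.2%: 1.383.
- 5% to 6%: 1.213.

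**3. Away from those rates the limits part.** With land odds o = p/(1−p), the risk at the OR limit is OR·o/(1 + OR·o). The land rates in this table are illustrative assumptions, not figures from the article.

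| Outcome, OR limit | Land rate | Difference at the OR limit | Stated margin |
|---|---|---|---|
| Infant, 1.21 | 3% | 0.61 points | 1.0 |
| Infant, 1.21 | 7% | 1.35 points | 1.0 |
| Parous, 1.38 | 1% | 0.37 points | 0.6 |
| Parous, 1.38 | 3% | 1.09 points | 0.6 |

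For example, at an infant land rate of 7% the odds at the limit are 1.21 × 0.07/0.93 = 0.0911. The risk is 0.0911/1.0911 = 8.35%, an excess of 1.35 points.

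**4. Power if the OR limit decides, at the planning rates and sizes.** Standard error of ln OR = √[2/(n p(1−p))]; power = Φ(ln(OR limit)/SE − 1.645).

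| Test | ln(limit) | SE | Power, OR limit | Simulated, OR | Power, difference | n per group for 90% on OR |
|---|---|---|---|---|---|---|
| Nulliparous | 0.2070 | 0.0780 | 84.4% | 84.3% | 89.9% | about 9110 |
| Parous | 0.3221 | 0.1301 | 79.7% | 79.4% | 90.0% | about 10 490 |
| Infant | 0.1906 | 0.0721 | 84.1% | 84.1% | 89.9% | about 9925 |

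The simulation used 400 000 studies per outcome with a Wald 90% interval for the OR. Rounding of the limits explains little of the shortfall: with unrounded limits the OR power is 84.5%, 80.2% and 84.9%.

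**5. Off the planned rate** (same formulas, infant outcome, 8100 per group). At 3%, power is 98% on the difference and 66% on the OR. At 7%, it is 80% on the difference and 93% on the OR. The gap can go either way.

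**6. Larger groups.** The Sample size section takes 25% of waterbirths as nulliparous and regards nulliparous waterbirth as the scarcest of the four groups. At that ratio, 7500 nulliparous waterbirths bring 7500 × 3 = 22 500 parous waterbirths. With 22 500 against 7500 parous land births, SE = √[(1/22 500 + 1/7500)/0.015744] = 0.1063, and OR power is Φ(0.3221/0.1063 − 1.645) = 91.7%.

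**The case against.** Read literally, the criterion is the difference: the OR stands only in brackets, the margins are absolute, and the primary analyses are described as comparing proportions. On that reading the 90% power is right. A reader might infer from step 4 that the stated power is wrong and is really 84%, 80% and 84%. The article does not support that: the sample sizes reproduce, and the lower figures apply only if the OR limit decides.

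It may also be said that a logistic model can yield an interval for the difference, and that how it does so is detail for the analysis plan, which is not shown. That is fair for the method of derivation. It does not remove the problem, because the article itself fixes two unequal thresholds for each test.

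The maternal figures are values at the minimum group size. If the parity ratio of 1:3 also holds among low-risk waterbirths, parous power on the OR is 91.7%, so the 80% is not a forecast. Nulliparous land births are also expected to exceed 7500, by an unstated amount; about 11 600 would restore 90%. The article nevertheless gives 15 000 waterbirths and 15 000 land births as its target, and the parity argument does not help the infant figure. More births raise power but do not make the two limits equivalent.

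Finally, the land rates of 3% and 7% are not in the article, and they cut both ways. They show the direction and size of the mismatch, not an expected result.

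**Conclusion.** The point holds as a defect in the stated decision rule. Each primary criterion is worded for the difference but carries an OR limit that agrees with it only at land rates of 4.6%, 1.6% and 5%, and the only interval said to be calculated is for the OR. At assumed infant rates of 3% and 7%, OR 1.21 stands for 0.61 and 1.35 points, so it can be stricter or more lenient than the 1.0-point clinical margin. In a safety study the lenient direction matters more.

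The power consequence is conditional. It is 90% on the difference, as stated. If the OR limits decide, it is about 84% (nulliparous), 80% (parous) and 84% (infant). These figures assume an unadjusted OR, equal true rates, equal groups and exactly the planned sizes. An adjusted OR is conditional on the covariates, so its correspondence with a marginal risk difference is looser still.

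**What to change.** State in the Main analysis section that the absolute risk difference alone decides non-inferiority for all three tests. Obtain its two-sided 90% interval from the unadjusted and adjusted logistic models by marginal standardisation, with a delta-method or bootstrap standard error. Remove the bracketed OR limits from the decision rule, or label them as illustrative at the assumed land rates, and report ORs descriptively. This keeps the clinical margins and the scale on which the study was sized.

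Keeping the OR limits as the criterion would also give a single rule, but the sample size or the stated power would then need revision and the margin would no longer be a fixed absolute excess. The recommended change costs wording and one post-estimation step, with no new data.
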